### Data collection and management

A database management system will be used for data collection and management. Telephone and inhouse screening data will be directly entered into the database. Drawing items of the MoCA and the CES-D 10 will be performed on a paper sheet and item responses will be immediately entered into the database. For baseline and follow-up assessments, an electronic case report form (eCRF) will be used. Following the intervention sessions, machine-readable paper questionnaires will be used and personally transferred to the database manager on a regular basis. The database management system will set reminders for the collection of fall calendars, activity diaries, and activPALs: Once any of these items are overdue, the study coordinator will be notified. Participants’ individual identifiers and identifiable information will be kept on encrypted local servers at the two study sites as well as in the database, accessible only by authorized study personnel and—upon request—the external study monitor. Only research staff directly involved in data analysis will have access to the final dataset.

### Study monitoring

Quality assurance and control of the study will be performed by an external study monitoring institute being entirely independent of the coordinating investigator and institutions involved in the study conduct. This will include regular monitoring visits in every study centre, partial source data verification, continuous monitoring of the eCRF entries for 50% of the patients during the clinical part of the study, and checks for completeness and plausibility of eCRF.

### Statistical analyses

Statistical analyses will follow the ICH Harmonized Tripartite Guideline “Statistical Principles for Clinical Trials” E9 [64]. Based on the trial of Clemson et al., we expect a decrease in fall incidence (expressed as falls per amount of PA) of 79.4% for LiFE [29]. A one-sided Pearson’s chi-square test will be used to test noninferiority with α = 0.05 in the fall incidence between LiFE and gLiFE with a noninferiority margin of − 15.9%.

All main analyses will be done according to the intention-to-treat principle, which will include all randomized participants in the analysis dataset for whom a baseline assessment was conducted, regardless of their adherence to and compliance with the assigned treatment. Participants who withdrew or dropped out are requested to participate in follow-up assessments; those who are lost to follow-up will be included in the full analysis set by imputing their missing data. Secondary analyses will provide a more detailed insight on which dimensions both treatments are effective to deepen the understanding of trial results. Understanding the underlying physiological pathways in both formats will increase knowledge on the effectiveness of the intervention components and strategies and thereby improve the design and implementation of both LiFE treatments. Additionally, sensitivity analyses will be performed to explore the effect of missing values and attrition during treatment:Per-protocol analysis of the dataset restricted to all participants with available measurements for the primary variables and no protocol violations.If the number of missing values is substantial (higher than 5% for a given variable), a sensitivity analyses will be conducted for imputing missing values.

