### Sample size

The sample size was calculated using Pearsons’s Chi-square test, yielding *N* = 81 participants per group to be able to show noninferiority between treatments, accepting a non-inferiority margin of 20% difference to the reduction demonstrated in the original LiFE study [29]. Considering a drop-out rate comparable to the original LiFE study of 25% for all assessments [29], actually *N* = 108 participants per group are needed. To account for an additional variance due to the multi-centre design we increased the sample size by 10% and added another safety margin, coming out with an envisaged sample of a total of *N* = 300 community-dwelling participants to take part in the study: *n* = 150 at both study sites, i.e., the Network Aging Research (Heidelberg, Germany) and the Robert Bosch Hospital (Stuttgart, Germany).

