The LiFE program—as an exercise approach focused on the modification of individuals’ behaviour—has shown its effectiveness in a large randomised controlled trial, and it has been explicitly recommended for implementation as part of therapy practice to reduce fall risk in one of the aforementioned systematic reviews [67]. LiFE has shown its superiority relative to placebo and structured exercise [29], so assuming that LiFE *is* effective, the next step would be to look at its suitability for the recommended implementation on a large scale. Because LiFE requires seven individual one-to-one home visits, the program’s feasibility and affordability in everyday practice can be challenging. An economic evaluation of the LiFE program or a less costly alternative has never been conducted, despite the fact that the impact on both health outcomes and costs needs evaluating across competing interventions to enable well justified allocation decisions [52]. Therefore, a group-based LiFE approach should be tested for its noninferiority compared to the original, individually delivered LiFE program. Noninferiority trials aim to determine whether one treatment is not worse than a reference treatment by a predefined acceptable amount [32]. This kind of research is conducted on the premise that the “new” treatment has some other advantage compared to the reference treatment, for example less invasiveness and greater ease of administration [32]. In our study, gLiFE’s noninferiority in terms of fall incidence is evaluated with reference to the original LiFE program (LiFE): gLiFE will be recommended if it is not worse than LiFE by more than the predefined margin (∆ = 15.9%). As only a few studies of fall-related interventions have assessed costs and effects (e.g. in terms of QALYs) [70], and results were heterogeneous [73, 74], economic evaluations are needed to guide health care resource allocation.

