Although Clemson and colleagues adhered to the common practice of evaluating fall prevention trials based on fall rates per total observation time (e.g., falls per person year) [29], in this study, we will estimate falls per risk exposure time, i.e., per walking duration and energy expenditure. Considering that, as the LiFE program promotes PA then it also enhances risk exposure of participants, the relationship of PA and falls might be a more adequate outcome rather than the rate of falls per total observation time [26, 75]. This is more likely an appropriate analysis considering that both physical inactivity and high falls risk are negatively associated with healthy life expectancy [76].

As a limitation, it has to be acknowledged that in such a trial, it cannot immediately be distinguished between effective and ineffective treatment due to the lack of (placebo or “sham”) control, i.e., both treatments/interventions could be ineffective [77]. However, the LiFE study by Clemson et al. has shown its high value and effectiveness, even though in only one large trial.

Concluding, this study will be of high practical relevance as noninferiority of gLiFE would facilitate nationwide implementation due to lower financial and personnel requirements. This is of special importance in the face of the large number of older people in need of preventive measures which have to be provided by a small number of therapists, especially when it can be expected that the ratio of therapists to patients will increase. Due to the lack of knowledge on the participants’ personal (home) environment and the consequential limitation of individualization options of LiFE activities in the group (gLiFE), we do not expect the group format to be superior to LiFE. However, LiFE activities are graded and individually adapted to each gLiFE participant’s functional level, also taking into account personal routines and environment as described by the participant, and using simulated demonstration instead of demonstration in the actual situation as provided in LiFE. Unlike LiFE, utilizing LiFE in a group may also enrich the program’s prosperity through psychosocial resources such as social interaction and mutual role-modelling of the participants [78, 79].

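### The noninferiority margin is in percentage points of a decrease in fall incidence with no defined reference, not on the scale of the primary outcome, and the basis of the 79.4% behind it is not reconciled

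*Protocol article*

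**What the plan says.** All places are in the Protocol article.

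- **Primary outcome measures:** fall incidence is the number of falls in relation to total energy expenditure. Falls come from monthly calendars over 12 months and activity from a thigh-worn accelerometer.
- **Sample size:** the calculation is made "accepting a non-inferiority margin of 20% difference to the reduction demonstrated in the original LiFE study". Its result is described as "yielding *N* = 81 participants per group to be able to show noninferiority between treatments". A 25% dropout rate takes this to 108 per group. A 10% multi-centre allowance and a further safety margin lead to 300 in total.
- **Statistical analyses:** from the original trial, "we expect a decrease in fall incidence (expressed as falls per amount of PA) of 79.4% for LiFE". The planned test is then named: "A one-sided Pearson’s chi-square test will be used to test noninferiority with α = 0.05". The margin stated for this test is −15.9%.
- **Discussion, decision rule:** "gLiFE will be recommended if it is not worse than LiFE by more than the predefined margin", with the same 15.9% given as the margin.
- **Discussion, metric of the original trial:** its authors "adhered to the common practice of evaluating fall prevention trials based on fall rates per total observation time". Counting falls per exposure is presented as what this study does differently. The same section acknowledges that there is no placebo or sham control.

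**The concern.** A noninferiority margin has to be on the scale of the contrast that the trial estimates. This trial observes a falls-per-energy-expenditure rate in gLiFE and in LiFE, so the natural contrast is the ratio or difference of those two rates. The margin is instead a number of percentage points of a reduction, and a reduction needs a reference. There is no untreated arm and no reference incidence is defined.

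The 79.4% that generates both the margin and the sample size is described as falls per amount of activity. Elsewhere the article says the trial it comes from used falls per observation time.

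The recommendation of gLiFE depends on this threshold. Unless its scale is fixed, analysts could apply different limits to the same data and reach opposite conclusions.

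**Working it through.** **Inputs.** LiFE reduction 79.4%, margin 15.9%, one-sided α = 0.05 and Pearson chi-square test (Statistical analyses); margin rule of 20% of the reduction, 81 per group and 25% dropout (Sample size). Power is not stated; 80% is assumed.

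**1. What the margin is.** 0.20 × 79.4 = 15.88, which rounds to 15.9. The margin is therefore in percentage points of the reduction.

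**2. Reproducing the plan's figure.** Treat 79.4% as a binomial proportion in both arms, with true difference 0 and an absolute margin:

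n = (z₀.₉₅ + z₀.₈₀)² × 2 × p(1 − p) / margin²
= (1.645 + 0.842)² × 2 × 0.794 × 0.206 / 0.1588²
≈ 80.2, rounded up to **81 per group**.

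A margin of 0.159 also gives 81 after rounding up. Then 81 / 0.75 = **108**. The other settings tried do not give 81:

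| Setting | n per group |
|---|---|
| Same formula, 85% power | 94 |
| Same formula, 90% power | 111–112 |
| Same formula, one-sided α = 0.025, 80% power | 102 |
| Pooled test of 79.4% vs 63.5%, one-sided, 80% power | 99 |
| Pooled test of 79.4% vs 63.5%, two-sided, 80% power | 126 |

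So the arithmetic is sound for its inputs, but a reduction in a rate has been entered as if it were a proportion of participants.

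**3. Is there a reference for the decrease?** Both arms are active. Table 4 lists fall history for the past 12 months at telephone screening, and accelerometry at baseline, 6 and 12 months. A before-after figure would set recalled falls against calendar falls. Past falls are also a route into the trial (Eligibility criteria), so regression to the mean would enter. The article describes no such before-after calculation.

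**4. What the margin tolerates on the rate-ratio scale.** Assume that LiFE achieves 79.4% and that both reductions refer to one common incidence.

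- Smallest gLiFE reduction still acceptable: 79.4 − 15.9 = 63.5%.
- Remaining incidence: 36.5% in gLiFE, 20.6% in LiFE.
- Ratio: 0.365 / 0.206 = **1.77**.
- Effect retained: 63.5 / 79.4 = 80% in points; ln 0.365 / ln 0.206 = **64%** on the log scale.

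**5. Dependence on the true LiFE reduction.** Hold 15.9 points fixed and let r be the true reduction. The tolerated ratio is (1 − r + 0.159)/(1 − r), and the share of the effect given up is 0.159/r. All values of r other than 79.4% are assumptions.

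| r | Tolerated ratio | Effect given up, in points |
|---|---|---|
| 30% | 0.859/0.700 = 1.23 | 53% |
| 50% | 0.659/0.500 = 1.32 | 32% |
| 70% | 0.459/0.300 = 1.53 | 23% |
| 79.4% | 0.365/0.206 = 1.77 | 20% |

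One fixed number of points therefore corresponds to quite different limits on the observable contrast.

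**6. The source of 79.4%.** Statistical analyses labels it falls per amount of activity and bases it on the original trial. The Discussion says that trial evaluated falls per observation time. No step from one metric to the other is shown.

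**The case against.** The test is described as a comparison between LiFE and gLiFE, and 79.4% is introduced as an expectation, so it can be read as a planning value only. The effect measure may be set out in an analysis plan not shown. That plan could settle the estimator, but the article itself fixes the margin and makes it the rule for recommending gLiFE, on a scale that does not match its own endpoint.

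A reader might infer that the margin cannot be computed from the trial's data at all. That goes too far: a crude before-after figure could be formed from recalled falls and baseline activity, and activity after baseline also rests on short recording periods. What stands is that no reference is defined and that this one would be weak.

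A reader might also infer that 79.4% is wrong. The documents do not show that. The Background reports that the original trial both enhanced activity and reduced falls, so a secondary derivation is possible, and its report is not available here. What stands is that the derivation is missing and that the two sections need reconciling.

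Finally, retaining 80% of the effect in points rather than on the log scale is a choice, not an error, and the absence of a control arm is openly acknowledged. Both are granted. Neither supplies a margin for the rate comparison.

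**Conclusion.** The point holds as a mismatch between margin and endpoint. The decision threshold is 15.9 points of a reduction with no defined reference, while the trial compares two falls-per-energy-expenditure rates. The sample size reproduces on a binomial reading, given 80% power, which is an assumption. The metric of the 79.4% is described in two ways that must be reconciled.

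The ratio of 1.77 is conditional on LiFE achieving 79.4% and on a common reference for both arms. It concerns falls per unit of activity, so it should not be read as saying that the plan would accept 77% more falls. At assumed reductions of 30% to 50% the same margin implies 1.23 to 1.32. A purely relative between-arm reading of 15.9% would give 1.16, but neither the 20% rule nor the reproduced 81 supports it.

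**What to change.** Before unblinding, amend the protocol or analysis plan as follows.

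1. State the margin as a value that the upper confidence limit of the gLiFE:LiFE rate ratio of falls per energy expenditure must not exceed.
2. Derive that value from the original trial's LiFE-versus-control effect in the metric that trial reported, or show how 79.4% falls per activity was obtained. Reconcile Statistical analyses with the Discussion.
3. Take the word *decrease* out of the decision rule, and use the same margin in Sample size, Statistical analyses and Discussion.
4. Restate the power or sample-size basis for that rate comparison at the planned 300 participants.

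No particular ratio is prescribed here. Retaining 80% of the effect on the log scale would give exp(−0.2 × ln 0.206) = 1.37, but only if 79.4% stands, and that is looser than the 1.23 to 1.32 implied at reductions of 30% to 50%. It is an illustration only.

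No new data collection is needed. The cost is an amendment, and restated power that may be lower than the current calculation suggests.

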### Aims

We hypothesize in this multi-centre, two armed, single-blinded, randomised noninferiority trial that: *(1)* gLiFE won’t be less efficacious than LiFE in terms of reducing fall incidence expressed as number of falls per PA, i.e., energy expenditure; gLiFE won’t result in a lower intervention retention rate (i.e., percentage of the sample completing the 6-month and 12-month follow-up assessment) as compared to LiFE; *(2)* delivering gLiFE will be cost-effective and less costly compared with LiFE; *(3)* in both groups, physical performance in terms of strength and balance as well as physical activity will be enhanced at comparable levels.

A process evaluation according to guidelines of the Medical Research Council (MRC) for complex interventions [31] will be performed in order to assess quality of implementation and to identify causal mechanisms as well as contextual factors which may affect study outcomes.

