#### Primary outcome measures

Fall incidence: expressed as number of falls in relation to total energy expenditure. Clinical relevance and sensitivity of this combined index has been validated recently in a cohort of 1214 community-dwelling older adults in Germany [26].

Falls will be assessed based on the fall definition provided by Lamb et al. [43], using an established procedure, i.e., a fall calendar which is returned to the respective study centre on a monthly basis for a period of 12 months. If a person has fallen, information on date, time, injuries and subsequent treatment related to the fall, location of the fall, and movement during which the person has fallen has to be provided on the sheet. In congruence with recommendations [15], a telephone-interview will be performed to rectify missing data, to ascertain details on injuries, and to confirm the current health status of the person. Injurious falls will be categorized according to a standardized system [44].

Physical activity will be assessed using “activPAL4™ micro” accelerometers (PAL Technologies Ltd., Glasgow, Scotland). It is a light, small sized (45 × 25 × 5 mm) triaxial accelerometer worn on the central front thigh over a period of 9 consecutive days (i.e., 7 days with complete data over 24 h). Body posture (sitting/lying, standing/upright) and walking activity are derived from raw data. The device has shown good to excellent reliability [45, 46] and criterion validity in identifying metabolic equivalent of task values [47] as well as body postures [48].

Cost-effectiveness: Cost-effectiveness will be assessed by the incremental cost-effectiveness ratio (ICER) represented by the ratio of the difference in costs and the difference in health effects between both interventions. Costs include in- and outpatient treatment, formal and informal care, transportation and medication as well as intervention costs due to labour costs, room hires, transportation of staff and participants, and material costs. Health effects are measured using quality-adjusted life years (QALYs) based on the EQ-5D-5 L [49, 50]. German values sets for the EQ-5D-5 L have been published recently [51]. The concept of QALYs is commonly used in health economic evaluation for measuring health effects. It combines health-related quality of life with length of life and enables comparing health effects across different diseases [52].

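### The primary noninferiority test (one-sided Pearson chi-square) and the sample size treat as a proportion an endpoint defined as falls per unit of physical activity

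*Protocol article*

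**What the plan says.** Endpoint. Under Primary outcome measures the fall outcome is given as "Fall incidence: expressed as number of falls in relation to total energy expenditure". Aims words the hypothesis the same way: "reducing fall incidence expressed as number of falls per PA, i.e., energy expenditure". Falls come from "a fall calendar which is returned to the respective study centre on a monthly basis for a period of 12 months", so one person can contribute several events. The Discussion explains why falls per observation time is not used and says "we will estimate falls per risk exposure time, i.e., per walking duration and energy expenditure", which adds a second denominator.

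Test. Statistical analyses begins the test sentence with "A one-sided Pearson" and continues: "chi-square test will be used to test noninferiority", applied to fall incidence in the two arms at α = 0.05. The margin is −15.9%, and the expected LiFE effect is a 79.4% decrease in falls per amount of activity.

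Sample size. This section also names the Pearson chi-square test and arrives at 81 per group, 108 after 25% dropout, and a planned total of 300. The margin is 20% of the reduction seen in the earlier LiFE trial.

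The article names no count or rate model, no exposure offset and no rule that turns falls into a yes/no outcome.

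**The concern.** The endpoint is a count of recurrent events divided by a continuous exposure that differs between people. A Pearson chi-square test works on a table of counts of independent units. It has no place for an activity denominator or for repeat falls in one person. To run it, the analyst has to do one of two things that the article does not choose between:

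- classify each person as faller or non-faller, which is a different endpoint; or
- count every fall as an independent unit, which ignores that some people fall much more often than others.

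This one test decides whether gLiFE is recommended (Discussion). With the choice left open, it could be made after the data are seen. In a noninferiority trial an understated variance favours the positive conclusion.

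**Working it through.** **1. Reproducing 81 per group.** Inputs: 79.4% and 15.9% (Statistical analyses), one-sided α = 0.05, equal true effects. Power is not stated; 80% is assumed. For a noninferiority comparison of two proportions:

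n = 2(z₀.₉₅ + z₀.₈₀)² × p(1 − p) / Δ² = 2(1.645 + 0.842)² × 0.794 × 0.206 / 0.159² ≈ 80.0, just above 80, so 81.

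With the unrounded margin 0.20 × 0.794 = 0.1588 the result is 80.2, again 81. Then 81/0.75 = 108, as stated.

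Other settings do not give 81: 90% power gives 111; one-sided 0.025 gives 102; a comparison of 0.794 with 0.635 gives 99 one-sided and 126 two-sided; unpooled variance at 0.794 and 0.635 gives 97.

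So the arithmetic is right for a proportion of participants with an absolute margin. But 79.4% is described as a relative decrease in a fall rate, and such a quantity has no p(1 − p) variance.

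**2. Route A: faller yes/no.** A margin-shifted test of two proportions with 150 per arm and a true difference of 15.9 points rejects in about 4.5–5% of simulated trials for control proportions of 0.5 to 0.794. The error rate holds, but the question changes. For negative binomial falls with mean μ and dispersion k, P(no fall) = (1 + kμ)^(−1/k). Take μ = 1, k = 1 (assumed): P = 0.500. Subtracting 0.159 leaves 0.341, which corresponds to a rate of 1/0.341 − 1 = 1.93. A 15.9-point loss of non-fallers is then a rate ratio of 1.93. Over μ = 1.0 or 1.66 and k = 1 or 2 the ratio runs from about 1.9 to 2.6.

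**3. Route B: falls as independent events.** The article states no ratio margin. One reading is that gLiFE must keep 80% of the 79.4% reduction: 0.80 × 0.794 = 0.6352, and (1 − 0.6352)/(1 − 0.794) = 0.3648/0.206 = 1.77. Let M = 1.77 be the true ratio and μ the LiFE rate, with constant exposure. Per person, the variance of the log rate ratio is V₁ = 1/μ + 1/(μM) if falls are independent, and V₂ = V₁ + 2k with overdispersion. The false-noninferiority rate is Φ(−1.645 √(V₁/V₂)).

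| μ, k (assumed) | V₁ | V₂ | By formula | Simulated, 150 per arm |
|---|---|---|---|---|
| 0.5, 1 | 3.13 | 5.13 | 9.9% | 9–10% |
| 1.0, 1.5 | 1.56 | 4.56 | 16.8% | 15–17% |
| 1.5, 2 | 1.04 | 5.04 | 22.7% | 22–23% |

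With 112 per arm, after 25% dropout, the simulated rates are about 8–10%, 16–17% and 22–23%. A test on the same data that uses between-person variance rejects in about 5–6%. If the assumed rate is given to gLiFE instead, V₁ = (1 + M)/μ = 5.54, 2.77 and 1.85, and the formula gives about 8%, 13% and 18%.

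**4. What a rate analysis would need.** n per arm = 2(z₀.₉₅ + z₀.₈₀)²(1/μ + k)/(ln M)², with 80% power, true ratio 1, μ = 1.0 or 1.66 and k = 0.5 to 2 (all assumed). At M = 1.77 this gives 42–114; at M = 1.20 it gives 411–1116. The plan would analyse 150 × 0.75 ≈ 112 per arm. Clustering within gLiFE groups is not included.

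**The case against.** The strongest counter-argument is that the plan's own arithmetic points to Route A. Since 81 follows from a margin-shifted comparison of proportions, a reader who infers that the primary test necessarily has an invalid error rate goes further than the article allows. On that reading the error is close to 5%, and the 9–23% belongs to the route that the sample size supports less. This stands: the inflation is conditional on how the test is run.

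A reader might also infer that the test is for equality and so cannot address noninferiority. The article does not support this as a separate fault. It gives one-sided testing, a margin and a decision rule, and the exact statistic can be left to an analysis plan. Likewise, the absence of a covariate list is not an error in itself, and the article does provide for imputation and adds 10% to the sample for the multi-centre design.

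Finally, 1.77 is one reading of the margin, and the simulation holds exposure constant, so it does not imitate the per-activity endpoint. Both limits stand.

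None of this removes the mismatch. Route A drops repeat falls and activity, which the Discussion gives as the reason for choosing this outcome, and no yes/no outcome is defined anywhere in the article.

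**Conclusion.** The point holds as a mismatch between endpoint, test and sample size that is fixed in the article's text, not merely detail left to an analysis plan. No reading of the named test validly tests falls per unit of activity. On faller yes/no the 5% error can hold, but a difference at the 15.9-point margin corresponds to a fall rate ratio of about 1.9–2.6 under assumed rates and dispersion, and the activity-adjusted hypothesis is not tested. On falls counted as independent events, the nominal 5% becomes roughly 9–23%, given LiFE rates of 0.5–1.5 falls per year, dispersion of 1–2 and a ratio margin of 1.77, all assumed.

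A reader might go on to infer that the trial is underpowered for the stated endpoint. The article does not settle this. At a ratio margin of 1.77 about 112 analysed per arm roughly covers the range computed; at 1.20 it falls far short. The answer depends on a margin that has not been stated on the rate scale.

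**What to change.** Before unblinding, amend the primary analysis as follows:

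- **Model.** Replace the chi-square test with a negative binomial or robust-variance Poisson model of each person's fall count, adjusted for site and falls in the prior 12 months (collected at telephone screening). The variance should allow for clustering in the gLiFE groups of 8–12.
- **Exposure.** Prespecify one denominator and use its log as offset. Energy expenditure (Primary outcome measures) and walking duration (Discussion) must be reconciled.
- **Margin and decision.** State the margin as a rate ratio, for example 0.3648/0.206 = 1.77 if the intent is to keep 80% of the reduction, and justify it. Declare noninferiority if the upper one-sided 95% confidence limit of the gLiFE:LiFE rate ratio lies below it.
- **Supporting analysis.** Keep faller yes/no in this role.
- **Sample size.** Restate the power that N = 300 gives for this analysis, with the assumed fall rate, dispersion, dropout and clustering.

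No new data are needed. The costs are an amendment, a wider confidence interval than one that treats falls as independent, and a restated power that may be less favourable.
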